##### Exercise self-regulation

The participant’s self-regulation for exercise will be assessed using the behavioral regulations in exercise questionnaire version 2 (BREQ2) [33] on three occasions. This five level-Likert scale-questionnaire has 19 items assessing exercise self-regulation which consists of five categories: external, introjected, identified, intrinsic and un-motivated [33]. The psychometric properties of the BREQ2 is adequate to assess self-regulation for exercise in breast cancer survivors [47].

##### Exercise barrier and task self-efficacy

The nine item rating barrier self-efficacy scale will be used to assess the confidence of participants performing exercise when experienced some difficulties. Task self-efficacy will be assessed with a four items scale. This questionnaire was validated and tested for internal consistency in women with breast cancer during treatment period [34]. Efficacy beliefs will be assessed at the start and end of the trial (see study outcomes measurement in Table 1).

**Table 1 Tab1:** Study outcomes measurement for both groups of participant

Outcome measurement	Method	Week 1 Baseline (T1)	Week 12 (T2)	Week 24 (T3)
**Primary outcomes**				
Psychology health	DASS-21	x	x	x
QoL	FACT-B version 4 questionnaire	x	x	x
Immune cell functions	Isolation of peripheral blood mononuclear cells	x	x	x
**Secondary outcomes**				
Daily step count/Average activity volume assessment	Step count tracker	x	x	x
Adherence in pedometer usage	Step count tracker wearing time with data capture (daily hours and the number of wearing days)		x	x
Exercise self-regulation;	BREQ2	x	x	x
Exercise barrier and task self-efficacy	Exercise barrier and task self-efficacy rating scale	x	x	x

### Statistical methods

#### Sample size estimation and justification

Based on a power of .8, alpha of .05 and large effect size in change in FACT-B (Cohen’s d = 2.23) from previous studies [48] we calculated that a minimum of 53 participants are required. Considering a 10–20% drop-out rate in exercise studies we decided to recruit a minimum of 64 participants (*n* = 32 in each of the two conditions).

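### The minimum of 53 participants does not follow from power 0.8, alpha 0.05 and d = 2.23, and the target of 64 falls slightly short of the quoted 20% drop-out

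*Protocol article*

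**What the plan says.** The justification is two sentences in the Protocol article, Statistical methods, Sample size estimation and justification. The first gives the error rates ("Based on a power of .8, alpha of .05") and then the effect and the result together: "large effect size in change in FACT-B (Cohen’s d = 2.23) from previous studies [48] we calculated that a minimum of 53" participants. The second raises this for attrition: "Considering a 10–20% drop-out rate in exercise studies", and then "we decided to recruit a minimum of 64 participants", which is 32 per group. The Abstract and the Recruitment section repeat 64, and Recruitment says that it comes from the power calculation. No other sample-size reasoning appears in the article. The section does not say whether the test is one- or two-sided, whether d is a between-arm or a within-person quantity, or which test and time point the calculation refers to.

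**The concern.** The inputs and the result are printed side by side, so the calculation can be repeated, and a standardised effect above 2 needs only a handful of participants. A requirement of 53 therefore looked too large by a factor of about five. If so, either d is not 2.23 on the scale implied, or 53 came from inputs that are not stated. In both cases a reader cannot learn from this section what effect on FACT-B the trial is sized to detect, which is the purpose of a sample-size statement. The step from 53 to 64 also looked short for a 20% loss.

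**Working it through.** **Inputs from the section:** power 0.80, alpha 0.05, d = 2.23, required N = 53, drop-out 10–20%, target 64 (32 per group). The 1:1 allocation is from the Randomisation section. **Assumption:** two-sided test; one-sided was also tried.

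**1. Trying to reproduce 53.**
- Two-sample, normal approximation: n per arm = 2(1.960 + 0.842)² / 2.23² = 2 × 7.85 / 4.97 = 3.16, so 4 per arm and 8 in total.
- Two-sample, exact noncentral t: 4 per arm gives power 0.748 and 5 per arm gives 0.869, so 10 in total. One-sided: 8 in total.
- Paired t: n = 4 gives power 0.832.
- 2×2 crossover (N − 2 degrees of freedom, within-person correlation 0, 0.5 or 0.8): 4 to 6 in total.
- Two-sample with alpha Bonferroni-split over 3, 15 or 100 tests: 12, 18 or 22 in total.
- Two-sample with power raised to 0.999: 24 in total.

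None of these comes near 53. With d = 2.23 and 53 participants, the power of the two-sample test exceeds 0.9999.

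**2. What 53 would detect at 80% power, two-sided 5%.**
- Between arms, 26 and 27: the normal approximation is d = 2.802 × √(1/26 + 1/27) = 2.802 × 0.2748 = 0.770. The exact t gives 0.785, written below as 0.79 because 0.78 gives only 79.5% power. One-sided: 0.69.
- Uncontrolled pre-post change in 53: the normal approximation is 2.802 / √53 = 0.385. The exact t gives 0.392.

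**3. Drop-out.**
- Needed to keep 53: 53 / 0.90 = 58.9, so 59; 53 / 0.85 = 62.4, so 63; 53 / 0.80 = 66.25, so 67.
- Left from 64: 64 × 0.90 = 57.6; 64 × 0.80 = 51.2, so 51.
- Largest loss that keeps 53: 1 − 53/64 = 17.2%.
- Between-arm detectable d (exact t, two-sided): 0.71 with 64 (32/32), 0.785 with 53 (26/27), 0.80 with 51 (25/26).

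**4. Baseline adjustment, with 53 evaluable.** The 0.785 is in SDs of change. If the SD is equal at T1 and T2 and the correlation is r, the SD of change is √(2(1 − r)) SDs of the T2 score. Both figures below are in SDs of the T2 score, and r is assumed because the article gives no value.

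| r | change score: 0.785 × √(2(1 − r)) | baseline-adjusted: 0.785 × √(1 − r²) |
|---|---|---|
| 0.5 | 0.785 (0.79) | 0.68 |
| 0.6 | 0.70 | 0.63 |
| 0.7 | 0.61 | 0.56 |

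**The case against.** On the stated inputs the discrepancy runs towards too many participants: if d = 2.23 were right, 64 would be ample. The remedy leaves enrolment unchanged, and anyone can work out a detectable effect from 64 once a contrast is chosen. All of that is true. It limits the harm but does not make the calculation correct, and the choice of contrast is exactly what the section leaves open.

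A reader might go further and infer that the trial's known sensitivity is a between-arm d of about 0.8. The article does not support that as fact. It describes a crossover with three assessments, plans linear mixed models (Analysis of data), and states its aim as the effect of 24 weeks of activity combined with motivational interviewing (Study goals and objectives), which both arms receive. The figure of 0.79 holds only for a two-sided comparison of change between arms.

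A reader might also call 2.23 an implausible effect. The cited source is not at hand, so it cannot be settled whether 2.23 is a misprint, a raw mean difference, a within-group value or a true standardised effect. What can be shown is that it does not lead to 53.

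On drop-out, the section quotes a range and does not promise to cover its upper end. The target covers 10%, the 15% midpoint and up to 17.2%. At 20% loss, power at d = 0.785 falls only from 80% to 78.4%. That 53 × 1.2 = 63.6 rounds to 64 suggests multiplication where division was needed, but this is an inference about working that is not shown.

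**Conclusion.** The point stands as an error in the printed calculation. With d = 2.23, power 0.8 and two-sided alpha 0.05, the requirement is 10 participants (two-sample) or 4 (paired), not 53. One-sided testing, a crossover analysis, multiplicity adjustment and much higher power do not close the gap. This conclusion does not depend on which contrast was meant. It should be corrected because it is the article's only sample-size justification.

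The detectable effect for 53 does depend on the contrast: about 0.79 between arms on change, or about 0.39 for an uncontrolled pre-post change, both two-sided at 80% power. The drop-out shortfall is real but minor: 51 evaluable instead of 53 at 20% loss, which moves the between-arm figure from 0.785 to 0.80.

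It would go too far to conclude that too few are enrolled. The article states no effect, other than 2.23, against which 64 could be judged inadequate.

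**What to change.** Rewrite the paragraph as follows.

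- Remove d = 2.23 as the basis for 53, or correct it if it is a misprint or on another scale.
- Name the contrast, time point, test and sidedness.
- State what 64 delivers over the quoted drop-out range. If the contrast is between arms on FACT-B change at T2, two-sided 5%, 80% power, the text could read: d about 0.71 with all 64, 0.79 with 53 evaluable and 0.80 with 51 evaluable (20% loss). If another contrast is intended, recompute these for it.
- Keep the 10–20% range and add that 64 retains 53 up to about 17% loss. Narrowing the range to fit the target would only conceal the shortfall.
- If a baseline-adjusted figure is added, give both values in SDs of the T2 score and state the assumed correlation. With 53 evaluable, adjustment lowers the detectable difference from 0.79 to 0.68 at r = 0.5, from 0.70 to 0.63 at r = 0.6, and from 0.61 to 0.56 at r = 0.7.

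No extra participants are needed. The rewording is one paragraph, but naming the contrast is a design decision that the investigators must make; it cannot be supplied by an editor.

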#### Analysis of data

Baseline descriptive statistics (mean, standard deviation for continuous data and percentage for categorical data) will be used to describe the distribution of personal data and variables between two groups of participant (e.g., age, breast cancer health history, body compositions, and blood pressure). Independent T-test will be used to compare means for continuous data and the Pearson Chi square will be used for testing the difference in distribution of a categorical variable at baseline [49].

Linear-mixed models will be used to identify the relationship between physical activity volume by step counting and mental health (DASS-21), QoL (FACT-B), self-regulation (BREQ2) and self-efficacy at T1, T2 and T3; the relationship between activity volume by step counting and immune biomarker changes at T1,T2, and T3. The models will also be used to control for the effect of covariates or confounding factors and to manage for missing data.

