**Methods:**

The study will recruit 64 female breast cancer survivors within 3 years of diagnosis and at least 6 months post primary treatments at Western Health Sunshine Hospital, Melbourne, Australia. They will be randomly allocated to immediate intervention (IIG group) or delayed intervention groups (DIG group) in a 1:1 ratio. All participants will be given a wearable device (Fitbit Alta HR) and undertake self-directed physical activity for 24 weeks and will receive MI for 12 weeks (IIG; during week 0 to week 12 and DIG; during week 13 to week 24). Participants’ daily step count and the changes of immune cell functionality will be assessed at the beginning (week 1: T1), week 12 (T2) and week 24 (T3) of the program. Physical activity adherence will be assessed at T2 and T3. Participants will also complete four questionnaires assessing exercise self-regulation (BREQ2), exercise barrier and task self-efficacy, mental health (DASS-21) and QoL (FACT-B) at three time points (T1 to T3). Linear-mixed models will be used to assess the relationship between physical activity volume by step counting and mental health (DASS-21), QoL (FACT-B), immune biomarkers, self-regulation (BREQ2) and self-efficacy at T1, T2 and T3;between 2 groups.

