### Study goals and objectives

The study has an overall aim to determine the effects of 24 weeks self-directed activity combined with motivational interviewing on (i) psychological health (depression, anxiety, stress), (ii) quality of life (QoL; physical, social/family, emotional and functional) and (iii) immune function in female breast cancer survivors. In addition, we will explore the dose-response relationship between exercise volume (step count) and the outcome measures.

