## Methods of intervention

### Self-directed physical activity

Participants will perform a 24-week period of self-directed, pedometer controlled physical activity [38, 39]. All participants will be given a step-count tracker devise (Fitbit Alta HR) and investigators will explain the prescribed pedometer-based activity to participants. Fitbit Alta HR is a wearable gadget and can be used to monitor step count. The participants’ activity engagement will be accompanied by individual face-to-face and phone call MI [22]. Participants will be taught how to operate the Fitbit and will be taken on a 10 min walk to experience a moderate level of exertion.. At week 1 (baseline or T1), all participants will be prescribed to assess and record their activity using the Fitbit monitoring device through its application via computer or smartphone to establish their baseline physical activity volume by step count. Following this, they will be advised to perform their activity on their own pace as tolerated and will wear the Fitbit during the daytime or when they are available for physical activity throughout the 24 weeks. Individual participants will be advised and motivated to gradually increase their daily steps on physical activity at moderate intensity exertion or at their perception of taking some efforts but can talk during physical activity (the recommendation by the department of health, Australian government) [40] during face-to-face and over the phone MI. The participants will be advised for safety during physical activity. They will be suggested to stop physical activity if adverse symptoms occur such as chest pain or pain down to arms, dizziness, difficulty breathing, unusual rapid heart rate, and sever fatigue. The researcher will suggest to the participant to inform their family members and take a mobile phone with them before they go out to exercise. They will be also advised to take record of their daily steps in their notebook. All participants will be informed that the researcher will track the participants’ step count and tracker usage time via Fitbit connect application. Individual average daily step count, and activity level will be assessed at baseline (T1), week 12 (T2), and week 24 (T3).

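### The planned step-count mixed models do not separate within-woman from between-woman association, so a single step term could show a dose-response that reflects only stable differences between women

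*Protocol article*

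**What the plan says.** Under Study goals and objectives, the article adds to its main aim that "we will explore the dose-response relationship between exercise volume (step count) and the outcome measures".

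The model that serves this objective is in the Analysis of data section: "Linear-mixed models will be used to identify the relationship between physical activity volume by step counting and mental health (DASS-21), QoL (FACT-B", followed by BREQ2 and self-efficacy, at T1, T2 and T3. For the immune outcomes the same section speaks of "the relationship between activity volume by step counting and immune biomarker changes at T1,T2, and T3". On adjustment it says only: "The models will also be used to control for the effect of covariates or confounding factors and to manage for missing data". The abstract repeats the model and ends its outcome list with "immune biomarkers, self-regulation (BREQ2) and self-efficacy at T1, T2 and T3;between 2 groups".

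On the exposure, the section on self-directed physical activity says "Individual average daily step count, and activity level will be assessed at baseline (T1), week 12 (T2), and week 24 (T3"), so each woman contributes up to three step values, one of them at baseline. Steps are not assigned: after the baseline week "they will be advised to perform their activity on their own pace as tolerated". Only the timing of motivational interviewing is randomised.

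Nowhere does the article say how step count is coded in the model, or whether the slope of interest is between women or within a woman.

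**The concern.** Step count measured three times per woman carries two kinds of information. One is how active she habitually is compared with other women. The other is how her activity moves around her own level. Each has its own slope against the outcome. In a random-intercept model with step count as one time-varying term, the coefficient is a weighted average of the two slopes.

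Here the between-woman slope is open to obvious confounding. Women who feel better or are fitter may walk more and score better at every visit, including T1, where any association can only be a comparison between women. Visit, arm and arm-by-visit terms do not remove this, and unnamed covariates remove it only as far as they happen to capture habitual activity.

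Two errors are possible. A significant step coefficient may be read as evidence that walking more helps when a woman's own changes in steps do nothing. Or, if the between-woman association runs the other way, a real within-woman relation may be hidden.

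**Working it through.** **The plan's own figures.** The article gives no figure for the dose-response analysis. Its sample size rests on "Based on a power of .8, alpha of .05 and large effect size in change in FACT-B (Cohen’s d = 2.23) from previous studies", which concerns FACT-B change and not the step coefficient. I take the 64 women recruited and the 53 required as given; how 53 was derived does not bear on this point.

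**Inputs.**
- From the article: n = 64 or 53, three visits, two arms 1:1, alpha 0.05 (taken as two-sided).
- Assumed, because the article gives none: the share of variance lying between women (ICC) for steps and for outcome, and the correlation r between a woman's habitual steps and her habitual outcome. Both variables are scaled to SD 1, and the true within-woman effect is set to zero.

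**Approximate formula, both ICCs 0.7.**
- Variance of a woman's mean steps over three visits: 0.7 + 0.3/3 = 0.8.
- Between-woman slope on means: r × 0.7/0.8, which is 0.2625 for r = 0.3 and 0.4375 for r = 0.5.
- The random-intercept model discounts between-woman information by 0.3/(0.3 + 3 × 0.7) = 0.125.
- Information per woman: between 3 × 0.8 × 0.125 = 0.30; within 2 × 0.3 = 0.60. Weight on the between-woman slope: 0.30/0.90 = 1/3.
- Blended coefficient: 0.2625/3 = 0.0875 for r = 0.3; 0.4375/3 = 0.146 for r = 0.5.
- Standard error at n = 64: √(0.3/(64 × 0.90)) = 0.072.
- Expected z: 1.21 and 2.02. Chance of |z| > 1.96: about 23% and 52%.

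**Simulation.** REML random-intercept model with visit and arm-by-visit terms, 1,500 trials per setting, both ICCs 0.7. Rejection rate of the single step term when the within-woman effect is zero:

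| r | n = 64 | n = 53 |
|---|---|---|
| 0 | 6.2% | not run |
| 0.2 | 13.1% | 15% |
| 0.3 | 24.5% | 24% |
| 0.4 | 41.9% | 39% |
| 0.5 | 59.2% | 55% |

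With steps split into person mean and deviation, the deviation term rejects in 5.6% to 5.7% of trials at n = 64.

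A separately coded simulation (visit and arm terms, 1,000 trials per setting, n = 64, ICCs 0.7) gives 5.3%, 25.8% and 58.5% at r = 0, 0.3 and 0.5 for the single term, and 5.0%, 6.2% and 6.1% for the deviation term. Its mean single-term coefficients, 0.090 and 0.159, are close to the formula. The formula runs slightly low because the step term absorbs some woman-level variance, which raises the between-woman weight.

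**Sensitivity to the ICCs.** With ICC 0.5 to 0.85 for steps and 0.5 to 0.7 for outcome, n = 64, the single term rejects in 19% to 41% of trials at r = 0.3 and 33% to 84% at r = 0.5. At n = 53 the ranges are 15% to 35% and 30% to 77%. The deviation term stays at about 4% to 7% throughout.

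**Masking and precision.** With a true within-woman slope of 0.3 SD per SD, n = 64 and ICCs 0.7, power for the single term against the deviation term is 34% against 90% at r = −0.3, 76% against 90% at r = 0, and 97% against 91% at r = 0.3. The last pair shows the price of splitting when the two slopes roughly coincide.

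**Immune markers.** If the outcome is change from baseline, a woman's stable outcome level cancels. Simulated with a single step term against change at T2 and T3, rejection was 3.6% to 6.5% at r = 0.3 and 0.5, so no inflation.

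**The case against.** The strongest reply is that the article does not commit the error. A reader might infer that it enters raw step count as one term; it does not say so. It names the exposure, outcomes, visits and model class, and a split into person mean and deviation would fit its wording. How a time-varying covariate is coded is commonly left to the analysis plan. The adjustment sentence also leaves room for baseline steps as a covariate.

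A reader might also infer that the objective is a test that changing a woman's steps does not change her outcome. The article states no such null. It offers an exploratory dose-response and a relationship, so it would be too strong to say that a stated objective goes unanswered.

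The size rests on assumed ICCs and correlations and vanishes at r = 0. The simulated visit-level noise is independent of the outcome, so the deviation term holds 5% by construction. In practice a woman who feels better may then walk more, which biases the within-woman slope too.

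All of this stands and limits the point. It does not remove it. The article fixes step count against outcome at visits that include baseline, for a self-selected exposure, and the most natural fit of that specification gives the blended slope. The stated safeguard names no covariate. On the immune clause the reply may hold in full, although that clause includes T1, where no change from baseline exists, and the abstract lists immune biomarkers without mentioning change.

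**Conclusion.** The point holds in a conditional form, as a cheap improvement. The stated step-count models for DASS-21, FACT-B, BREQ2 and self-efficacy do not distinguish within-woman from between-woman association. If step count enters as a single term, a significant coefficient cannot be read as what follows when a woman changes her steps. With no within-woman effect, 64 women, ICCs of 0.7 and a between-woman correlation of 0.3 to 0.5, the false-positive rate for that reading is about 25% to 60%; over the wider ICCs tried at those correlations it is 19% to 84%. None of these ICCs or correlations comes from the article.

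The documents do not support saying that the trial will use a single raw term, that its dose-response finding will be false, or that the immune analyses are affected whichever way they are coded.

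**What to change.** In the models of the Analysis of data section, enter two step-count terms: each woman's mean step count over her visits, and her deviation from that mean at each visit. Keep visit and arm in the model. State that the exploratory dose-response statement rests on the deviation (within-woman) coefficient, and report the person-mean coefficient as a descriptive association. State also whether immune markers are analysed as levels or as change from baseline.

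Baseline steps plus change from baseline should not be treated as an equivalent coding. One baseline week is a noisy measure of habitual activity, so the change term still carries between-woman signal. In simulation it rejected in about 7% to 11% of trials at correlations up to 0.5, and its power was 83% against 92% for person-mean centring.

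The cost is one model term and a sentence or two of text, using step data already planned. Some precision is lost when the two slopes coincide (91% against 97% power above). The within-woman slope can still be confounded by factors that change over time, so the report should not present it as proof of causation.

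### Every outcome model described has step count as its explanatory variable, so the randomised comparison that serves the main aim has no stated test

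*Protocol article*

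**What the plan says.** Study goals and objectives puts the intervention first: "The study has an overall aim to determine the effects of 24 weeks self-directed activity combined with motivational interviewing on" psychological health, quality of life and immune function. Step count comes second: "In addition, we will explore the dose-response relationship between exercise volume (step count) and the outcome measures".

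Under Randomisation, both arms follow the self-directed activity programme for 24 weeks. What is randomised is the timing of MI: weeks 1 to 12 in the immediate group (IIG), weeks 13 to 24 in the delayed group (DIG).

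Analysis of data names between-group tests only at baseline: a t-test for continuous variables, and "the Pearson Chi square will be used for testing the difference in distribution of a categorical variable at baseline". The outcome models follow: "Linear-mixed models will be used to identify the relationship between physical activity volume by step counting and mental health (DASS-21), QoL (FACT-B", then BREQ2 and self-efficacy, and for the immune outcomes "the relationship between activity volume by step counting and immune biomarker changes at T1,T2, and T3". It adds: "The models will also be used to control for the effect of covariates or confounding factors and to manage for missing data". No covariate is named.

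The abstract describes the same step-count models and ends the outcome list with "self-regulation (BREQ2) and self-efficacy at T1, T2 and T3;between 2 groups".

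**The concern.** The objective called additional has the only outcome model, and the overall aim has none. This is more than detail left to an analysis plan. The article does fix the explanatory variable, in both places where it describes the model, and that variable is step count.

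Step count cannot stand in for the randomised arm. Self-directed physical activity says that women walk at their own pace as tolerated and are encouraged during MI to raise their daily steps. Table 1 lists step count as a secondary outcome. It is therefore measured after randomisation, chosen by the participant, possibly on the pathway from MI to outcome, and likely to share causes with mood and quality of life. The Background itself names tiredness as a barrier to activity.

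Two errors are at stake: a significant step coefficient when neither MI nor walking does anything, and a real MI effect missed because it acts through counselling rather than through steps.

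**Working it through.** The protocol gives no figure for this point, so there is none to reproduce.

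**The text side by side**

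| Place | Intervention effect | Step-count relationship |
|---|---|---|
| Study goals and objectives | overall aim | additional exploration |
| Analysis of data | baseline tests only | model for every outcome listed |
| Abstract, Methods | two groups mentioned, no arm effect defined | same model |

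**Inputs.** From the protocol: 64 women, 32 per arm, three visits, alpha 0.05 (taken as two-sided), 53 as the minimum required before drop-out. Assumed, because the document gives no figures: outcome variance 1, with intraclass correlation 0.6 (person variance 0.6, visit variance 0.4); person-level correlation c between activity and well-being of 0, 0.3 or 0.5; MI effect 0.65 SD; MI effect on steps of 0 or 0.5 SD.

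**Model as described.** Outcome on step count and visit with a random intercept per woman, and no effect of MI or steps on the outcome. Rejection rate of the step coefficient at nominal 5% (ranges are over repeat simulations):

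| c | step model | arm added as covariate | baseline-adjusted arm test at T2 |
|---|---|---|---|
| 0 | 5–6% | 4% | 5–7% |
| 0.3 | 22–23% | 22% | 5–7% |
| 0.5 | 48–54% | 51% | 5–7% |

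Adding arm only as a covariate changes nothing, because the shared cause lies between women within each arm. If step count is split into each woman's mean and her deviation from it, the within-woman term stays at 5–8%.

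**Hand check at a single time point.** For an observed steps–outcome correlation r and n = 64, power is about Φ(atanh(r) × √61 − 1.96).
- r = 0.2: 0.203 × 7.81 = 1.58; Φ(−0.38) = 0.35 (simulated 36%).
- r = 0.3: 0.310 × 7.81 = 2.42; Φ(0.46) = 0.68 (simulated 69%).

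These exceed the mixed-model rates because r here is the correlation actually observed. A person-level correlation is diluted by visit-to-visit variation, and the mixed model also weighs within-woman changes, which carry no association in this scenario.

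**Real MI effect of 0.65 SD.** Baseline-adjusted arm comparison at T2:
- Residual SD = √(1 − 0.6²) = 0.80.
- 64 women: SE = 0.80 × √(1/32 + 1/32) = 0.20; 0.65/0.20 = 3.25; power Φ(3.25 − 1.96) = Φ(1.29) = 0.90 (simulated 87–90%).
- 53 women: SE = 0.80 × √(4/53) = 0.22; 0.65/0.22 = 2.96; power Φ(1.00) = 0.84 (simulated about 83%).

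Step-count model, same effect: about 5–9% if MI does not move steps; 34–38% if MI raises steps by 0.5 SD and DIG receives MI in the second period.

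**The case against.** The strongest reply is the abstract. It attaches two groups to the same models, so arm may be meant to enter. Analysis of data lists no model terms at all, not even visit, so silence on arm is not a decision to exclude it, and an analysis plan not shown may hold the full specification. If the model had step count plus arm-by-visit, the 0.65 SD effect would be found in about 78% of runs, with 4–5% rejection under the null. The section also promises control for confounding, and speaks of a relationship, not an effect.

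Much of this stands, and it limits the point. A reader might infer that randomisation is discarded; the documents do not support that, because the abstract leaves room for a group term. A reader might also infer that the result will be a confounded association reported as an effect; open to confounding is as far as the text goes. Nor can it be said that the step model would nearly always miss a true MI effect, since detection depends on how far MI moves steps.

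What does not stand is that the abstract settles the matter. Its phrase qualifies a step-count relationship, defines no arm effect and is absent from the analysis section. Unnamed covariates do not restore the randomised contrast. An arm effect adjusted for steps would also leave out whatever MI achieves through walking.

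**Conclusion.** Wrong as written. The objectives, the abstract and Analysis of data do not agree on what is analysed, and the comparison that randomisation supports has no stated test. The model that is stated answers the exploratory question.

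The contradiction rests on the text alone. The sizes (roughly 23% and 50% false positives; 5–9% to roughly 35% detection against about 90%) are illustrative. They depend on the assumed intraclass correlation, correlations and MI effects; at c = 0 there is no excess of false positives. The 90% assumes that all 64 women are analysed.

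One limit belongs to the design. Because both arms receive the activity programme, IIG minus DIG estimates the effect of adding MI to self-directed activity. It does not estimate the effect of the combined programme named in the aim.

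**What to change.** Reconcile Study goals and objectives, the abstract and Analysis of data as follows.

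1. **Primary analysis.** A linear mixed model by randomised group with arm, visit and arm-by-visit terms, and the outcome's T1 value as covariate or constrained baseline.
2. **Reported effect.** The IIG-minus-DIG difference at T2, described as the effect of adding MI to self-directed activity. T2 is proposed because an effect of counselling may carry over into weeks 13 to 24.
3. **Supportive analysis.** A two-period crossover estimate, under a stated assumption of no carry-over. In the same illustration and without carry-over, it detects the effect in about 99% of runs, so the choice between the two is a real one and should be argued in the text.
4. **Exploratory analysis.** The step-count models, labelled as associations, with step count split into each woman's mean and her deviation from it.

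Cost: analysis wording only. Table 1 already schedules every variable needed. Choosing T2 over the two-period estimate is a design decision, to be made before outcome data are examined by arm.
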